#### Attendance and intervention completion

Retention rate (number and proportion that attended each class) of participants in MBCT-I group are documented. And reasons for non-attendance will be recorded. Participants who attended six or more iMBCT-I sessions will be considered as having completed the intervention. For those who did not complete the intervention, researchers would conduct interviews to inquire about the relevant reasons. In addition, the completion of the sleep diary, actigraphy usage, and the number of sessions attended are collected as indicators of adherence.

#### Safety assessments

We will record the possible adverse events in detail during the intervention period, including the time of occurrence, duration, and treatment measures of the adverse events. Common adverse events of iMBCT-I may include anxiety, emotional or physical discomfort, sleep disruption and daytime sleepiness, and these possible conditions will relieve or disappear as the intervention progresses. Serious adverse events will be reported to the Tongji Hospital of Tongji University Institutional Review Board in a timely manner.

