## Interventions

### Intervention description

#### Intervention group: iMBCT-I

Participants will receive a 12-hour iMBCT-I treatment. MBCT-I consists of weekly 1.5-h sessions over 8 weeks online through the Tencent Meeting, with mindfulness practice as homework six times a week.

The iMBCT-I program was adapted from the original format of Segal et al., which targeted mainly depression and consisted of eight 2.5-hour sessions held on a weekly basis (20). The modification mainly followed the MBCT-I in Wong SY and colleagues’ research, making it tailored for CID patients (22). Due to the limitation that Tencent Meeting displays a maximum of 25 members’ videos per page, we set the maximum group capacity to 20 individuals to ensure that all members can consistently maintain face-to-face interaction online.

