Participants in the SHE group will be attention-matched with those in the iMBCT-I group to control for expectancy and engagement effects. First, both groups will receive standardized informed consent, which clearly states: “This study compares two different approaches to improving sleep. You will be randomly assigned to one of the following: Program A – improving sleep through iMBCT-I, or Program B – improving sleep through SHE. Both are evidence-based, but it is currently unclear which is more suitable for most people.” This framing is intended to equalize treatment expectancy across groups. Second, both interventions will be delivered in an online group format via Tencent Meeting. Third, to maintain comparable levels of engagement and attention, participants in the SHE group will be asked to keep sleep diaries, just as in the iMBCT-I group. Research assistants will send daily reminders via smartphone to facilitate compliance. Considering that the iMBCT-I group will receive seven additional weeks of structured intervention, the SHE group will be administered seven weekly follow-up questionnaires to maintain engagement parity. These questionnaires will include items such as “How has your sleep been over the past week?” and “Which aspects of the sleep hygiene education have you applied?” Fourth, both groups will receive the same incentive: a free actigraphy upon completion of the study. Finally, post-intervention satisfaction assessments will be conducted for both groups to evaluate their subjective experiences with the respective interventions.

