### Adverse event reporting and harms

All adverse events reported by participants and observed by researchers, as well as causal assessments of adverse events following the intervention, will be recorded in the Case Report Form (CRF). MBCT-I is classified as a non-pharmacological treatment. To date, few instances have been identified that could potentially harm participants’ health (67, 68). The sleep restriction component (which involves reducing the time spent awake in bed to enhance sleep efficiency) may initially cause discomfort for participants. Other potential adverse reactions may include distress, anxiety, or exacerbation of insomnia during the psychotherapy process. All adverse events occurring during the study will be carefully monitored and documented to determine their relationship to the intervention.

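### Adverse events are given two different recording windows, and the described capture route depends on staff contact that differs between the arms

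*Protocol article*

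**What the plan says.** Two sections of the Protocol article describe adverse-event collection.

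- Safety assessments: "We will record the possible adverse events in detail during the intervention period". It goes on to list time of occurrence, duration and treatment measures. It names expected events for one arm only: "Common adverse events of iMBCT-I may include anxiety, emotional or physical discomfort, sleep disruption and daytime sleepiness".
- Adverse event reporting and harms: "All adverse events reported by participants and observed by researchers" are to be entered in the Case Report Form together with a causal assessment. The section closes with "All adverse events occurring during the study will be carefully monitored and documented to determine their relationship to the intervention".

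Contact with staff differs by arm. Under Intervention group: iMBCT-I, "Participants will receive a 12-hour iMBCT-I treatment", delivered as "weekly 1.5-h sessions over 8 weeks online through the Tencent Meeting". Under Control group: SHE, there is a single session of 1.5 hours, after which "the SHE group will be administered seven weekly follow-up questionnaires to maintain engagement parity". The same section gives SHE participants sleep diaries and daily smartphone reminders. The two example questionnaire items it prints concern sleep over the past week and use of the education. The trial is open-label (Blinding).

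**The concern.** The two statements on timing cannot both define the recording window. A team following Safety assessments could stop detailed recording at week 8. A team following the harms section would continue to week 20. Counts of events by arm mean something only when the window is fixed and common to both arms.

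The capture route raises a second question. What participants mention and what researchers see both depend on how often, and in what form, the two meet. The expected events (anxiety, discomfort, disrupted sleep, daytime sleepiness) are also ordinary complaints of people with chronic insomnia, so they can be expected in both arms. The harms section promises to judge whether events are related to the intervention, and the control arm is the natural benchmark for that. If events are easier to notice in one arm, the benchmark is distorted. An excess in iMBCT-I could then reflect better detection, more harm, or both.

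**Working it through.** **1. The recording window**

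- Trial design and Table 1 place the post-intervention assessment at week 8 and the last follow-up at week 20, with one calendar for both arms.
- Window under Safety assessments: weeks 0 to 8, reading the intervention period as that common calendar.
- Window under Adverse event reporting and harms: weeks 0 to 20.
- Difference: 20 − 8 = 12 weeks; 12 / 20 = 0.60, or 60% of the study.

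The section on criteria for discontinuing allocated interventions also refers to serious adverse events during the study, with no limit at week 8. That agrees with the wider window and not with the narrower one.

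**2. Contact by arm**

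- iMBCT-I: 8 sessions × 1.5 h = 12 h, which reproduces the stated total. An orientation session comes on top, but its length is not given.
- SHE: 1 session × 1.5 h = 1.5 h.
- Ratio of live time: 12 / 1.5 = 8 to 1.
- Scheduled weekly contacts over 8 weeks: 8 sessions in iMBCT-I; 1 session + 7 questionnaires = 8 in SHE. The ratio is 1 to 1.

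The arms therefore have equal numbers of scheduled weekly contacts, but of different kinds. In iMBCT-I all eight are live, so a researcher can observe and a participant can volunteer a complaint. In SHE one is live and seven are questionnaires, which capture an adverse event only if an item invites it.

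**3. Whether the SHE contacts ask about adverse events**

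The two printed items do not. They are given as examples, so an adverse-event item is neither shown nor excluded. Diaries and reminders are described as serving sleep recording and compliance.

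**4. Size of any imbalance**

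The document gives no adverse-event rate and no capture proportion for either arm. No risk ratio or bias can be calculated from it. Only the direction can be argued: less live contact, if it matters, would mean fewer recorded events in SHE.

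**The case against.** The strongest reply on the window is that the two sections can be nested: detailed recording during treatment and general monitoring throughout. Safety assessments does not say that recording happens only in the intervention period. That reading is possible, but the document does not state it, and nothing says what is recorded after week 8. A clarifying statement is still needed.

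On capture, the reply is stronger. The protocol deliberately equalises engagement through questionnaires, diaries and reminders. Anxiety and sleep are also measured identically in both arms by GAD-7, ISI, PSQI and actigraphy. Safety officers are to be contacted within 24 h of an adverse event, with no restriction by arm. The Case Report Form and full protocol are not shown, so the absence of an adverse-event form from a journal article is not in itself an error. No formal between-arm test of harms is planned in Statistical methods. All of this stands. It limits the point to a possible imbalance and does not establish one.

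Two stronger readings are tempting and are not supported. A reader might infer that the control arm is left largely unobserved, but the equal count of weekly contacts speaks against that. A reader might also infer that, because SHE is one session, its intervention period ends on day one and most of the first 8 weeks go unrecorded. Trial design, the diary schedule under Secondary outcome measures, and Table 1 all use one 8-week period without distinguishing arms.

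**Conclusion.** The point holds in two parts. First, the stated recording windows conflict by 12 of 20 weeks. This rests on the document's own wording and on reading the intervention period as weeks 0 to 8 in both arms. Second, the described capture route depends on contact, live contact is 8 to 1, and the SHE contacts are not described as asking about adverse events. Capture may therefore be unequal to an unknown degree. Any comparison of harms, or judgement of relatedness against the control arm, would be hard to interpret. The Discussion concedes unequal provider contact, but only as a non-specific influence on improvement in sleep, not as an influence on harms.

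No figure in the document is wrong on this point, and the primary ISI analysis is untouched. The change should be made because it improves the safety data at little cost.

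**What to change.** - Make Safety assessments and Adverse event reporting and harms state the same window in calendar weeks, from randomisation to week 20, identical in both arms.
- Put one short adverse-event question to both arms at the same times: the events already listed under Safety assessments plus an open category for other events. In SHE it can go into the existing weekly questionnaire; iMBCT-I participants receive an equivalent weekly item. Both arms answer it again at weeks 8 and 20.
- Report solicited and spontaneously reported events separately by arm, so that the solicited counts offer a like-for-like comparison.

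If the full protocol already contains such a question, it is enough to say so here and to correct the window. The cost is a wording change, one item set on the online platform already in use, and about a minute of participant time per week.

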### Sample size

With reference to the results of a large-scale randomized controlled trial conducted by Lee M. R. which compared the effects of online CBT-I with SHE on chronic insomnia patients, we estimated that the ISI score reductions in the iMBCT-I group and the SHE group were 7.7 and 3.1, respectively, with a common standard deviation of 5.5 (42). Assuming an alpha level of 0.05 and a power level at 0.9, the calculated minimum sample size was 30 participants per group. Estimating a dropout rate of 20%, we plan to recruit 80 participants in total.

## Assignment of interventions

Once recruitment is completed, eligible participants will be randomly allocated to either iMBCT-I group or SHE group with an allocation ratio of 1:1, using simple randomization facilitated by computer-generated random numbers in IBM SPSS 25.0 (66). The generated sequences will be placed in a sealed, opaque, identical-looking envelope, ensuring that the evaluator is unaware of the allocation. The study coordinator will assess baseline information and then inform the attending physician to refer participants to a research team. The study coordinator will not recruit participants.

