**Methods:**

This will be a two-armed, parallel group, randomized controlled study with 80 CID patients. The participants will be randomized to either the iMBCT-I program or the sleep hygiene education (SHE) program at an allocation ratio of 1:1 via simple randomization. Assessments will be carried out at baseline, at the end of the intervention (week 8) and at the follow-up time (week 20). The primary outcome was insomnia severity at week 8. Statistical analyses will follow the intention-to-treat (ITT) principle.

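### Simple randomisation of 80 people in one batch leaves arm sizes and sleep-medication balance to chance; a fixed 40/40 list stratified by medication use would cost almost nothing

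*Protocol article*

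**What the plan says.** The Assignment of interventions section states when allocation happens, "Once recruitment is completed, eligible participants will be randomly allocated to either iMBCT-I group or SHE group", and how, "with an allocation ratio of 1:1, using simple randomization facilitated by computer-generated random numbers in IBM SPSS 25.0". The Methods paragraph of the abstract repeats it: "at an allocation ratio of 1:1 via simple randomization". No blocking, stratification or fixed arm total is described. The Blinding section gives the task to a statistician outside the research team.

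The Sample size section sets the total: "Estimating a dropout rate of 20%, we plan to recruit 80 participants in total". In the section on the iMBCT-I group, therapy is delivered in online groups with a ceiling: "we set the maximum group capacity to 20 individuals". The number of groups is not given. The readable text does not state 40 per arm, although 80 at 1:1 implies it as the target; the flow chart is not shown.

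The Eligibility criteria admit both people who continue sleep medication unchanged and people who stopped it before enrolment. The Primary outcome analysis is a between-group test and a univariable regression on treatment group. The Sensitivity analysis adjusts for gender, age, marital status, education and baseline ISI, but not for sleep-medication use.

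**The concern.** Under simple randomisation each person is assigned independently with probability one half, so the size of each arm is a random quantity. Here that has two practical consequences.

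First, the number of capped, instructor-led groups to be run is unknown until allocation is done.

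Second, nothing in the allocation balances prognostic factors. Sleep-medication use is the clearest example: the protocol lets it differ between participants and records it at baseline, but neither the primary analysis nor the named sensitivity covariates take account of it. In an open-label trial of 80 people, a chance imbalance would complicate interpretation of the unadjusted result.

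Simple randomisation is usually preferred because the next assignment cannot be guessed as people enter one at a time. With everyone allocated together by an outside statistician, that advantage has nothing to act on.

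**Working it through.** **Inputs.** Total 80, 1:1, simple randomisation (Assignment of interventions; Sample size). Group cap 20 (iMBCT-I group section). For power: "the ISI score reductions in the iMBCT-I group and the SHE group were 7.7 and 3.1, respectively", "with a common standard deviation of 5.5", "Assuming an alpha level of 0.05 and a power level at 0.9", with 20% dropout (Sample size). The test is two-sided (Statistical methods).

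**The plan's own sample size.** The difference is 7.7 − 3.1 = 4.6.

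- Normal approximation: n per arm = 2 × [5.5 × (1.960 + 1.282) / 4.6]² = 30.04, which agrees with the stated 30.
- The t-based calculation gives 32 per arm.
- Allowing for dropout, 60 / 0.8 = 75 in total from the first figure and 64 / 0.8 = 80 from the second. The stated 80 is consistent with either the t-based figure or 75 rounded up.

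**Arm size.** Let X be the number in iMBCT-I, X ~ Binomial(80, 0.5). The mean is 40 and the SD is √(80 × 0.25) = 4.47.

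- P(X = 40) = 0.089
- P(X ≥ 41) = 0.456
- P(arms differ by 10 or more) = 2 × P(X ≤ 35) = 0.314
- The central 95% range of X is 31 to 49.

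**Groups needed.** With X of 41 or more, at least 41/20 rounded up = 3 groups are required.

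**Power after 20% loss in each arm (normal / t).**

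| Split | Power |
|---|---|
| 40:40 | 0.917 / 0.909 |
| 35:45 | 0.913 / 0.904 |
| 31:49 | 0.903 / 0.895 |

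Averaged over the binomial distribution of X, power is 0.914 / 0.905, a loss of about 0.3 to 0.4 points against a fixed 40:40.

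**Effective size.** For completers n₁ and n₂, the equivalent equal-arm size is 2n₁n₂/(n₁ + n₂).

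- 37:43: 2 × 29.6 × 34.4 / 64 = 31.8
- 30:50: 2 × 24 × 40 / 64 = 30.0

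The figure drops below 30 only when the smaller arm has fewer than 30 randomised. That probability is 2 × P(X ≤ 29) = 0.018.

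**Medication balance.** The documents give no proportion of medication users, so 20% to 50% (16 to 40 of 80) is assumed. With M users, the number of users in iMBCT-I is Binomial(M, 0.5) and the number of non-users is Binomial(80 − M, 0.5). The probability that the arms differ by 15 percentage points or more in medication use is 0.11 at M = 16 and 0.22 at M = 40. A fixed 40/40 total does not address this by itself; stratification does.

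**The case against.** The strongest reply is that simple randomisation is a recognised, unbiased method. It causes no type I error problem and no material loss of power, so preferring restricted randomisation is a matter of judgement. That stands, and the point is put here as an improvement, not as an error that invalidates the trial.

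Three stronger readings are tempting, and the documents do not support them:

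- A reader might infer that the stated 1:1 design cannot be achieved. Under simple randomisation, 1:1 means equal probability, and that is delivered.
- A reader might take 0.46 as the chance of overflowing the planned therapy capacity. The article gives a ceiling per group, not a number of groups or a limit of 40 places. A further group could absorb the excess.
- A reader might conclude that any arm of 37 or fewer leaves the trial short, because 37 × 0.8 = 29.6 is below the stated minimum of 30. This ignores the larger arm, which compensates.

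It can also be said that the team may intend to rank 80 random numbers and split them in half. That would give exactly 40:40, but it is a fixed-total allocation, so the text would then misname the method. Either way the wording needs changing, and because the method is named explicitly in two places this is not simply a detail left to another document.

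Finally, baseline ISI is adjusted for in the sensitivity analysis, and the mixed models include baseline covariates that are not named. Medication use might be among the latter, but those models are in the secondary analysis. Nor do the documents show that medication use is strongly prognostic. The case for stratifying on it rests on its being allowed to vary and on the low cost.

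**Conclusion.** The point holds as a low-cost improvement. As written, the allocation leaves arm sizes to chance: 0.09 for an exact 40:40 split, 0.31 for a difference of 10 or more, and 0.46 for more than 40 in iMBCT-I and so at least three capped groups. It also leaves baseline sleep-medication use unbalanced by design and unadjusted in the primary and listed sensitivity analyses. The benefit of changing it is predictable arm and group sizes and prognostic balance, not power.

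The arm-size figures assume exactly 80 people, each assigned independently. The medication-imbalance range of 0.11 to 0.22 rests on an assumed 20% to 50% of users. The argument that concealment loses nothing rests on allocation being one batch, as the Assignment of interventions section says.

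**What to change.** In the abstract and in Assignment of interventions, replace the simple-randomisation wording with a random permutation, by the independent statistician, of a fixed list of 40 iMBCT-I and 40 SHE assignments, stratified by baseline sleep-medication use (yes/no). If both strata are odd in size, give the extra place to opposite arms so that the totals stay 40/40. Include the stratum in the regression for the primary outcome and in the adjusted sensitivity model. State how many iMBCT-I groups will be run.

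If participants will in fact be allocated in waves, say so and use permuted blocks of concealed, varying size instead.

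The cost is one changed randomisation script, one model term and a short wording amendment. Medication use is already collected at baseline, so no new data are needed, and with batch allocation nothing is lost in concealment.

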## Blinding

This will be an open-labeled trial. Participants could not be blinded to treatment allocation as participants are notified of the two groups: iMBCT-I and SHE. Intervention leaders will be blinded to the group assignment and study hypotheses. A statistician who is not part of the research team will carry out the randomization and allocation procedure. The research team will have limited contact with the statistician to prevent allocation bias. The research assistant responsible for statistical analyses will be blinded to study hypotheses as well as randomization, assessment and intervention procedures.

## Data collection and management

Assessments will be conducted at week 0 (baseline), week 8 (post-intervention) and week 20 (3 months after intervention). Details are displayed in **Table 1**.

**Table 1 T1:** Assessment schedule.

Outcome	Measure	Time of assessment			
		Screen	Baseline (week 0)	Post-intervention (week 8)	Follow-up (week 20)
Socio-demographics	SR	X			
CID	MINI	X			
Insomnia severity	ISI	X	X	X	X
Sleep quality	PSQI		X	X	X
Mindfulness level	FFMQ		X	X	X
Depression	PHQ-9		X	X	X
Anxiety	GAD-7		X	X	X
Quality of life	SF-12	X	X	X	X
Attitudes	ATSPPH-SF	X	X	X	X
Dysfunctional beliefs	DBAS-16		X	X	X
Sleep parameters	Actigraphy		X	X	X
Treatment adherence	Number of completed sessions			X	X

SR-self reported measure; MINI- Mini International Neuropsychiatric Interview (MINI) provided by two psychiatrists; ISI- Insomnia Severity Index; PSQI- Pittsburgh Sleep Quality Index; FFMQ- The Five Facet Mindfulness Questionnaire; PHQ-9- The Patient Health Questionnaire-9; GAD-7- The Generalized Anxiety Disorder 7-item scale; SF-12- The 12-item Short Form Health Survey; ATSPPH-SF- The Attitudes Toward Seeking Professional Psychological Help Scale-Short Form; DBAS-16- Dysfunctional Beliefs and Attitudes about Sleep Scale 16-item version.

### Plans to promote participant retention and complete follow-up

Participants will be fully explained the importance of completing assessment at baseline, post-intervention and follow-up during recruitment. Each participant will receive a notification on the smartphone to complete the assessments online within 2 days. All questions were mandatory to ensure no missing data, and participants may pause and report to the research assistant at any time. Phone reminders will be provided if assessments were not completed on time.

